#### **Visit 4-14\*, week 4-40 (-60), duration 2 hours/visit: up-dosing OIT peanut**

The patient comes for up-dosing according to Table 3 with a predefined increase of peanut protein every 4-6th week up to 285 mg, maintenance dose (= 1.3 peanut = 3 pieces of Bamba), or the dose reached by the child after 60 weeks of up-dosing.

A physical examination is conducted, and a standardized questionnaire is filled in by the physician regarding physical status before the start of up-dosing. The diary is collected and reviewed. Only if the child has fully tolerated the previous dose and has not had any allergic side effects the last week, up-dosing is performed. The up-dosing is performed under the supervision of a research nurse and a physician at the study center. The child is observed for 90 minutes after the dose. The families/patients are informed about co-factors for allergic reactions e.g. high physical activity 3 hours after the dose intake. The up-dosing phase is ongoing for 40-60 weeks. If the patient becomes ill or cannot come to the study center after 6 weeks, the same dose is maintained until a new visit for up-dosing is made. If allergic reactions occur, the dose is changed according to Table 4. If for some reason (such as acute illness) the patient fails to take his/her OIT, the dose will change according to Table 5.

Between all the visits the families can contact the study nurse by telephone or mail if needed. If a moderate/severe allergic reaction/adverse event occurs during on-call time, the families are referred to one of Stockholm's children's emergency wards which will be informed about the study. Material for fecal samples is provided at visit 14.

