**Table 4. Action in dose-related symptoms outside the study center**

|                                                                                                                                                                                                                                                                                                                                                                                                                              |
|------------------------------------------------------------------------------------------------------------------------------------------------------------------------------------------------------------------------------------------------------------------------------------------------------------------------------------------------------------------------------------------------------------------------------|
| 
Mild symptoms 1: If the study physician considers the dose tolerated (e.g. only mouth itch), the patient may continue at the same dose at home. The dose can be divided into 2 doses (with 8-12 hours between). The patient may continue on this dose for another 1-2 weeks before dose increase.
                                                                                                              |
| 
Mild symptoms 2: If the study physician considers the dose as not tolerated the next dose should be reversed 1-2 steps and given at the study center.
                                                                                                                                                                                                                                                          |
| 
Moderate symptoms: The next dose should be given at the study center. Reverse 1-2 dose steps and continue at the lower dose until the patient has no or only mild symptoms.
                                                                                                                                                                                                                                    |

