| 
Severe symptoms 1 (max. 1 dose of adrenaline have been given): The next dose should be given at the study center. Reverse 2 dose steps. If no symptoms, continue with the lower dose in 2 weeks before the dose increase. If moderate or severe symptoms also occur at this dose, the patient should discontinue the treatment.
                                                                                |
| 
Severe symptoms 2 (2 doses of adrenaline have been given): The next dose should be given at the study center. Reverse 2 dose steps. If this works, continue with the lower dose in 6-8v before the next dose increase. If no symptoms, continue with the lower dose in 2 weeks before the dose increase. If moderate or severe symptoms also occur at this dose, the patient should discontinue the treatment.
 |

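### Table 4 gives two incompatible waits, 6-8 weeks and 2 weeks, before re-escalation after a home reaction needing 2 adrenaline doses

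*Protocol*

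**What the plan says.** The protocol's section on Visits 4-14 sends any change of dose after an allergic reaction to Table 4, whose title is "Table 4. Action in dose-related symptoms outside the study center". The gravest grade in that table is headed "Severe symptoms 2 (2 doses of adrenaline have been given". Its row has the next dose given at the center and the dose taken back 2 steps. It then gives one wait for a reduced dose that works and, in the next sentence, another for a child without symptoms: "continue with the lower dose in 6-8v before the next dose increase. If no symptoms, continue with the lower dose in 2 weeks". Moderate or severe symptoms on the reduced dose end treatment.

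The row above, Severe symptoms 1, covers reactions needing at most 1 dose of adrenaline. It contains the same 2-week sentence: "If no symptoms, continue with the lower dose in 2 weeks before the dose increase".

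For comparison, the Visits 4-14 section describes routine up-dosing as a "predefined increase of peanut protein every 4-6th week up to 285 mg", with a fallback to maintenance at 285 mg "or the dose reached by the child after 60 weeks of up-dosing".

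**The concern.** The two waits do not overlap, and their conditions are not mutually exclusive. A reduced dose that produces no symptoms has also worked, so a symptom-free child falls under both sentences. Two physicians following the protocol faithfully could hold the same child for 2 weeks or for 8.

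This matters because the rule applies to children aged 12-47 months at inclusion, after the most severe reaction the table grades, when that reaction happened outside the center. On the 2-week sentence the child goes up as quickly as after the milder grade. The step up itself is supervised, but the higher dose is then taken daily at home. The issue is dosing safety and uniform delivery of the intervention. Sample size and the definition of the primary outcome are not touched, since the protocol keeps a slower child on the dose reached by 60 weeks.

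**Working it through.** The contradiction is a matter of reading. Arithmetic only shows its size and what the longer hold would cost.

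**The two rows of Table 4 side by side**

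| Instruction | Severe symptoms 1 (at most 1 adrenaline dose) | Severe symptoms 2 (2 adrenaline doses) |
|---|---|---|
| Next dose at the center | yes | yes, same words |
| Go back 2 steps | yes | yes, same words |
| Hold if it works | none | 6-8 weeks |
| Hold if symptom-free | 2 weeks | 2 weeks, same words |
| Stop if moderate or severe symptoms recur | yes | yes, same words |

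Four of the five sentences in the second row repeat the first row. The 6-8 week hold is the only addition. If the 2-week sentence governs, the separate grade has no effect for a symptom-free child. That pattern suggests a sentence carried over from the row above, though the document does not confirm it.

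**Size of the conflict**

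- Difference in hold: 6 - 2 = 4 weeks to 8 - 2 = 6 weeks.
- Ratio: 6/2 = 3 to 8/2 = 4.
- Time back to the reaction dose, which is 2 steps up, assuming the second step takes the routine 4-6 weeks: 2 + (4 to 6) = 6-8 weeks on one reading, and (6 + 4) to (8 + 6) = 10-14 weeks on the other.

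**Can the 60-week up-dosing period absorb the longer hold?**

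Table 3b lists doses nr 4 to 14, from 3 mg to 285 mg. That is 11 doses and 10 increases. Without setbacks, 285 mg is reached at 10 × 4 = 40 weeks on the 4-week schedule and 10 × 6 = 60 weeks on a 6-week schedule.

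Suppose one event occurs after t weeks (0 to 4) at a dose, on the 4-week schedule. With hold h, the child needs h + 4 + 4 weeks to reach the next new dose, instead of the 4 - t weeks that remained:

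delay = (h + 4 + 4) - (4 - t) = h + 4 + t

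| Hold h | Delay | 285 mg reached |
|---|---|---|
| 2 weeks | 6 to 10 weeks | week 46-50 |
| 6-8 weeks | 10 to 16 weeks | week 50-56 |

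Both lie within 60 weeks. On a 6-week schedule starting from 3 mg there is no slack, so any setback leaves the child below 285 mg at week 60 under either wait. Children who start higher have more room. A child reacting at 250 mg starts near 250/4 = 62.5 mg. Even from the lower neighbouring step of 48 mg there are only 5 increases left, or 5 × 6 = 30 weeks.

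**How many children**

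The protocol gives no frequency for such reactions. If 2% to 10% of the 50 Group 1 children had one (an assumption), that is 0.02 × 50 = 1 to 0.10 × 50 = 5 children. The true number could be zero, and the contradiction does not depend on it.

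**The case against.** The best defence is a graded reading: 6-8 weeks if the reduced dose is tolerated with mild symptoms, 2 weeks if it causes none. It gives every sentence a purpose. The row stops treatment only for moderate or severe symptoms, so a mildly symptomatic child needs a rule, and the Moderate row of the same table does accept mild symptoms on a reduced dose. But Severe symptoms 2 does not draw that line, and on this reading a symptom-free child is still handled exactly as in Severe symptoms 1. What stands is that the intent is uncertain, so the clinical team has to settle it. A reading in which the two waits run one after the other fails, because each sentence ends at the dose increase.

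A second argument is that 2 weeks is not alarming. The first step up normally returns the child to a dose already tolerated before the reaction, and Table 5 allows re-escalation at intervals of at least one week. This does weaken the comparison with the routine 4-6 weeks, which governs steps to new doses. Table 5, however, concerns missed doses, not reactions.

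Third, safeguards exist. The first reduced dose is given at the center. Up-dosing requires that the previous dose was fully tolerated, with no allergic side effects in the last week, and is followed by 90 minutes of observation. Families hold an autoinjector, and the individual stopping criteria urge considering cessation after more than 2 anaphylactic reactions. These lower the risk, but none of them says how long to hold the dose.

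**Conclusion.** The point holds. The Severe symptoms 2 row prescribes both 6-8 weeks and 2 weeks for a symptom-free child, a gap of 4-6 weeks, and no other text in the protocol resolves it. The rule is operative, and the event it governs is serious but probably rare.

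The conclusion rests on reading 'v' as weeks, which is an inference, though no other unit fits well. The timing figures further assume a 3 mg start, a single event during up-dosing, and routine intervals after the first hold.

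**What to change.** Ask the clinical team to confirm that 6-8 weeks is the intended hold after a reaction needing 2 adrenaline doses. If so, delete the 2-week sentence from the Severe symptoms 2 row and write weeks in place of 'v'. The 2-week sentence stays in Severe symptoms 1. If two waits are really meant, keep both and state the condition for each, for example mild symptoms on the reduced dose versus none.

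The edit is one sentence in one table row. Its price is up-dosing that is 4-6 weeks slower for the few children affected. On the 4-week schedule one such event still leaves them within the 60-week limit.

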**Table 5. Action to missed OIT doses at home (e.g due to illness)**

| Number of missed doses in a row | Action                                                                                                  | Possible change in up-dosing interval                                                            |
|---------------------------------|---------------------------------------------------------------------------------------------------------|--------------------------------------------------------------------------------------------------|
| 1-2 missed doses                | Continue with the same dose.
The dose is taken at home.                                              | No change                                                                                        |
| 3-4 missed doses                | The next dose should be taken at the clinic but the dose can remain the same.                           | No change                                                                                        |
| 5-7 missed doses                | The next dose should be taken at the clinic and should be reduced to about 40-50% of the previous dose. | Up-dosing can be done more often (at least one week between) until the previous dose is reached. |
| >7 missed doses                 | The next dose should be taken at the clinic and should be reduced to about > 50% of the previous dose.  | Up-dosing can be done more often (at least one week between) until the previous dose is reached. |

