**Table 3b. Schedule for slow up-dosing: Starting dose is calculated from reaction dose at the baseline challenge**

| Dos nr | Amount of peanut protein, mg | Amount of peanut flour 10%* in mg (4,6% peanut protein) | Amount of peanuts, mg (one peanut approx. 800 mg) | Pieces of Bamba (700mg/piece, protein content 17,5%) | Interval, weeks | % increase |
|--------|------------------------------|---------------------------------------------------------|---------------------------------------------------|------------------------------------------------------|-----------------|------------|
| 4      | 3                            | 67                                                      | 11                                                |                                                      | 4               | 100        |
| 5      | 6                            | 133                                                     | 22                                                |                                                      | 4               | 100        |
| 6      | 12                           | 267                                                     | 44                                                |                                                      | 4               | 100        |
| 7      | 24                           | 533                                                     | 88                                                |                                                      | 4               | 100        |
| 8      | 32                           | 1067                                                    | 176                                               | 1/3                                                  | 4               | 100        |
| 9      | 48                           | 1578                                                    | 264                                               | 1/2                                                  | 4               | 50         |
| 10     | 95                           | 2111                                                    | 352                                               | 1                                                    | 4               | 33         |
| 11     | 144                          | 3200                                                    | 528                                               | 1,5                                                  | 4               | 50         |

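### As written, Table 5 allows a higher restart dose after more than 7 missed doses than after 5-7, reversing the table's own rising caution

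*Protocol*

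**What the plan says.** The protocol's section on Visits 4-14 (up-dosing) makes Table 5 the working rule: when a child "fails to take his/her OIT, the dose will change according to Table 5".

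Table 5 has four rows:

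- 1-2 missed doses: same dose, taken at home.
- 3-4 missed doses: "The next dose should be taken at the clinic but the dose can remain the same".
- 5-7 missed doses: at the clinic, and the dose "should be reduced to about 40-50% of the previous dose".
- More than 7 missed doses: "The next dose should be taken at the clinic and should be reduced to about > 50% of the previous dose".

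The last two rows share the same rule for climbing back: "Up-dosing can be done more often (at least one week between) until the previous dose is reached". Nothing else in the protocol corrects or overrides the last row.

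**The concern.** The first three rows move in one direction: same dose at home, same dose under supervision, reduced dose under supervision. The last row breaks that order. Its wording matches the row above except for the percentage, so the two can be compared directly: about 40-50% of the previous dose after the shorter gap, more than 50% after the longer one. The last row also sets no upper limit beyond being a reduction.

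This is a dosing-safety instruction for children with challenge-proven peanut allergy, and illness, which the table itself gives as an example, can cause such gaps. Staff who follow the text literally apply the less cautious rule after the longest interruption. Staff who notice the conflict must guess what was meant, so children with the same gap could restart at different doses.

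**Working it through.** **Inputs.** The percentages come from Table 5. The dose steps come from Table 3b: 3, 6, 12, 24, 32, 48, 95, 144, 190, 238 and 285 mg peanut protein. The maintenance dose is 285 mg. The plan gives no derived figure to reproduce; the check is direct arithmetic.

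**Step 1: the literal text at 285 mg.**

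- 5-7 missed: 0.40 × 285 = 114 mg to 0.50 × 285 = 142.5 mg.
- More than 7 missed: above 0.50 × 285 = 142.5 mg.

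The inversion does not depend on the dose, since both rows are percentages of the previous dose. At 144 mg, for example, the rows give 57.6-72 mg and then above 72 mg.

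**Step 2: which schedule steps the literal last row admits at 285 mg.** Assume restart doses are taken from the Table 3b steps, which Table 5 does not require.

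- 238/285 = 83.5%: admitted.
- 190/285 = 66.7%: admitted.
- 144/285 = 50.5%: admitted, and close enough to half that, with the word *about*, it also fits a corrected rule.
- 95/285 = 33.3%: not admitted.

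**Step 3: how typical a step near one half is.** Ten Table 3b levels have a lower step. In seven of them a lower step lies at 50-50.5%: 6 (3), 12 (6), 24 (12), 48 (24), 95 (48), 190 (95) and 285 (144). Only 32, 144 and 238 mg have none. At 238 mg the nearest steps are 144 mg (60.5%) and 95 mg (39.9%), so there the literal and corrected rules force different doses. At most levels they need not.

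**Step 4: the plausible corrections, at 285 mg.**

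| Reading | 5-7 missed | More than 7 missed |
|---|---|---|
| As written | 114-142.5 mg | above 142.5 mg |
| *By* for *to* in both rows | 142.5-171 mg | below 142.5 mg |
| *By* for *to* in the last row only | 114-142.5 mg | below 142.5 mg |
| Inequality sign reversed in the last row | 114-142.5 mg | below 142.5 mg |
| Rows swapped | above 142.5 mg | 114-142.5 mg |

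The 171 mg is 0.60 × 285. Each correction puts the last row at or below 50%. What differs between them is the 5-7 row. With *by* in both rows the ranges meet without overlapping (a cut of 40-50%, then a cut of more than 50%), which favours that reading but does not prove it.

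**The case against.** The strongest reply is that this is an obvious slip with little practical effect. A target of more than 50% with no ceiling makes poor sense as a dose, so a clinician would probably read it as a cut of more than half. Table 4 still carries an untranslated abbreviation for weeks ("If this works, continue with the lower dose in 6-8v before the next dose increase"), which suggests a translation error, and staff may have worked from a correct original that is not at hand. The restart is given at the clinic, and later increases are at least a week apart. At most dose levels a step at about half the dose satisfies both the literal and a corrected wording.

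Much of this stands. It limits the size of the problem and rules out several stronger inferences:

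- A reader might infer that children were given unsafe doses. The protocol does not show how staff applied the table, how often gaps of more than 7 doses occurred, or that any harm followed.
- A reader might take the forced gap at 238 mg as typical. It is not; it arises at three of the ten levels.
- A reader might conclude that every correction puts the last row strictly below 50%. Swapped rows give 40-50%, which reaches 50%.

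The reply does not remove the contradiction. The text as it stands is the less cautious rule and is the one the protocol tells staff to follow. Clinic supervision is also only a partial safeguard on paper: the up-dosing section says "The child is observed for 90 minutes after the dose", but that is stated for up-dosing visits, and Table 5 gives no observation time for a restart.

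**Conclusion.** The point holds: the last row of Table 5 is wrong as written and should be corrected. At 285 mg the literal text permits restarts of 190 mg (66.7%) or 238 mg (83.5%) after the longest gap, against 114-142.5 mg after a shorter one. If staff keep to about half the dose, the difference is small.

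Two assumptions lie behind these figures. The named doses assume restarts are taken from Table 3b steps. The 285 mg example assumes that Table 5 also governs maintenance: its title covers missed home doses generally, but the only cross-reference to it is in the up-dosing section. The inversion itself depends on neither.

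The documents do not settle which slip was made, so the intended 5-7 row remains open. The error bears on dosing safety and consistency of treatment; it does not touch the sample size or the primary analysis.

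**What to change.** Restate the last two rows of Table 5 together, in one convention, so that the row for more than 7 missed doses never exceeds 50% of the previous dose and is no less cautious than the 5-7 row. One suitable wording:

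- 5-7 missed: *reduced by about 40-50%*, a restart at 50-60% (142.5-171 mg at 285 mg).
- More than 7 missed: *reduced by more than 50%*, a restart below 50% (below 142.5 mg at 285 mg).

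The clinical team should confirm the 5-7 row. Changing only the last cell to *by* would remove the inversion, but it would leave adjacent rows in opposite conventions with overlapping ranges, since a restart at 40-50% would be allowed after either gap. The team should also say whether 144 mg (50.5% of 285 mg) counts as acceptable after more than 7 missed doses; if the limit is strict, the next Table 3b step is 95 mg (33.3%).

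The cost is two table cells and a notice to study staff. Design, sample size and analysis do not change.

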**Figure 1. SmaChO, peanut OIT timeline, group 1**

[figure not shown]

Supplement: SmaChO Study protocol [file mmc2.pdf]
